#### Alcohol use

Difference in grams of alcohol consumed per week, measured using Timeline Follow Back (TLFB), between groups up to 9-month follow-up. To be analyzed using an LMM with fixed effects for treatment, time and their interaction, a random effect for subjects and a random intercept. Restricted maximum likelihood estimation, Satterthwaite approximation, and a first-order autoregressive covariance matrix are to be used.

Data from baseline, sessions 1-12, 6- and 9-month follow-ups when TLFB was completed.

ITT and modified ITT as above.

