**Study population:** Up to one hundred and fifty treatment-seeking women, aged >18, diagnosed with DSM-5 PTSD and moderate to severe AUD.

**Method:** The study consists of three consecutive phases for each patient: *A screening and randomization phase*, carried out over the course of three to four visits, including diagnostic assessment and randomization 1:1 to receive COPE or RP, *a phase with cognitive and*

*behavioral therapy*, 12 sessions of COPE or 12 sessions of RP, typically one a week, and *a posttreatment follow up*, at session 12, and six and nine months post baseline.

**Outcomes:** The co-primary outcomes will be 1) change from baseline in PTSD symptom severity (Clinician-Administered PTSD Scale (CAPS-5)), measured after sessions 6 and 12 and six and nine months post baseline. 2) change from baseline in alcohol consumption per week (grams per week) and heavy drinking days (HDD) derived from Timeline Follow Back (TLFB), after therapy sessions 6 and 12 and six and nine months post baseline.

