## Study objectives

### Primary objectives

The co-primary objectives of the study are to determine whether COPE, in women with co-morbid PTSD and moderate to severe AUD, will:

-Reduce PTSD symptoms, measured as change from baseline, to post session 6, and 12, and six and nine months after baseline, compared to RP (measured using the Clinician-Administered PTSD Scale (CAPS))?

-Reduce alcohol use, measured as change from baseline in alcohol consumption per week (grams per week) and heavy drinking days (HDD) from baseline to session 6, and 12, and six and nine months after baseline, compared to RP?

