## COPE vs RP RCT statistical analysis plan 241022

One pre-selected model per outcome will be run. There will be no testing for differences at baseline.

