## Secondary outcomes

### Self-rated PTSD symptom severity

Measured using the PTSD Checklist – Civilian version (PCL-C), range 17-85. To be analyzed using an LMM with fixed effects for treatment, time and their interaction, a random effect for subjects and a random intercept. Restricted maximum likelihood estimation, Satterthwaite approximation, and a first-order autoregressive covariance matrix are to be used.

Data from baseline, sessions 1-12, 6- and 9-month follow-ups when PCL-C was completed.

ITT and modified ITT as above.

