### A biomarker of alcohol use

A biomarker of alcohol use (PEth) in blood. To be analyzed using an LMM with fixed effects for treatment, time and their interaction, a random effect for subjects and a random intercept. Restricted maximum likelihood estimation, Satterthwaite approximation, and a first-order autoregressive covariance matrix are to be used.

Data from baseline, mid-treatment (session 6) and the last treatment session (session 12), 6- and 9-month follow-ups when blood samples were taken.

ITT and modified ITT as above.

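### Heavy drinking days, one of the two measures in the protocol's second co-primary outcome, has no pre-specified analysis in the SAP, and no reason is given

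*Combined protocol and SAP*

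**What the plan says.** The protocol names HDD as part of the co-primary alcohol outcome in two places. Under Outcomes, the Summary gives the second co-primary outcome as "change from baseline in alcohol consumption per week (grams per week) and heavy drinking days (HDD) derived from Timeline Follow Back (TLFB", assessed after sessions 6 and 12 and at six and nine months. The Primary objectives section opens with "The co-primary objectives of the study are to determine whether COPE, in women with co-morbid PTSD and moderate to severe AUD, will", and its alcohol item is again "change from baseline in alcohol consumption per week (grams per week) and heavy drinking days (HDD) from baseline to session 6" and the later visits, compared with RP.

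The SAP opens with the rule "One pre-selected model per outcome will be run". Its co-primary Alcohol use section then covers one measure: "Difference in grams of alcohol consumed per week, measured using Timeline Follow Back (TLFB), between groups up to 9-month follow-up". The secondary outcomes are self-rated PTSD severity ("Measured using the PTSD Checklist – Civilian version (PCL-C), range 17-85"), "A biomarker of alcohol use (PEth) in blood", and PTSD remission. HDD is not listed at any level.

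**The concern.** If the SAP is followed as written, a measure that the protocol twice places among the co-primary outcomes yields no pre-specified result. An HDD analysis done later would be post hoc.

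The loss is not only formal. Grams per week measures volume, while HDD measures how often drinking is heavy. The protocol's account of TLFB, in the baseline assessment section, says it supports both kinds of variable. The Background frames the trial's hypothesis partly as a reduction in heavy alcohol use, and HDD is the measure closest to that. A treatment could move one measure and not the other, so a report on grams alone would not answer the alcohol objective as declared.

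Timing adds to this. The SAP, labelled 241022, already plans a modified ITT analysis that leaves out two participants found not to have had current PTSD at entry. Some participant-level baseline information was therefore known when the outcome list was settled. When a primary measure disappears at that stage without a recorded reason, readers cannot tell a principled simplification from a choice influenced by data.

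**Working it through.** No stated figure is in dispute, so the main check is a comparison of the two outcome lists.

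**Step 1. Compare the lists.**

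- Protocol, Summary (Outcomes): CAPS-5; then grams per week and HDD.
- Protocol, Primary objectives: CAPS; then grams per week and HDD.
- SAP, Co-primary outcomes: CAPS-5; grams per week.
- SAP, Secondary outcomes: PCL-C; PEth; PTSD remission.

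HDD is named as co-primary in two places in the protocol and in none in the SAP. The SAP's model rule does not cover it, because no HDD outcome is listed for a model to be attached to.

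**Step 2. Count correctly.** The protocol numbers two co-primary outcomes, and both domains remain in the SAP. What is missing is one of the two measures inside the second. The protocol does not say whether grams per week and HDD are separate tests, alternatives or one joint criterion. On any of these readings, the SAP does not analyse the outcome as declared.

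**Step 3. Check whether HDD can still be derived.** TLFB records daily drinking. It is taken for the past 90 days at screening and at six and nine months, and completed before each treatment session. Counts of heavy days can therefore be obtained, over windows of different length. Neither document states the gram or drink threshold that makes a day a heavy drinking day, so the variable is not yet defined.

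**Step 4. Cost of restoring HDD as a separate test (illustration only).** Neither document states an alpha or a multiplicity rule. Assume two-sided 0.05 per test and success claimed on any one test.

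- Two independent tests (CAPS-5, grams per week): 1 − 0.95² = 1 − 0.9025 = 9.75%.
- Three independent tests (adding HDD): 1 − 0.95³ = 1 − 0.857375 = 14.3%.
- Three tests with HDD and grams per week correlated, CAPS-5 taken as independent of both (simulation, 2,000,000 draws): 13.6% at correlation 0.5, 12.9% at 0.7, 11.7% at 0.9. These correlations are assumed.

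For jointly normal test statistics, independence is the worst case, so 14.3% is the ceiling under these assumptions. If all primary tests had to succeed, there would be no such inflation and the cost would fall on power instead.

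**The case against.** The strongest defence is that the SAP keeps the core of the outcome. Grams per week is itself a protocol-declared co-primary measure, not a substitute brought in later, and both co-primary domains are still analysed. The rule of one model per outcome may reflect a deliberate choice of a single alcohol measure, which would also limit multiplicity. Nothing forbids an HDD analysis, and the TLFB data are still collected. This stands in part: the grams analysis remains a declared primary analysis, and narrowing to one measure can be defended if it is documented. Here it is not documented.

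Three stronger readings are tempting, and the documents do not support them:

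- A reader might infer that HDD will never be analysed. The SAP shows only that no analysis is planned.
- A reader might infer that selective reporting has taken place. The two excluded participants show knowledge of baseline PTSD status, which is an eligibility matter. They do not show that drinking outcomes, arm-level data or HDD results had been seen. The SAP's past-tense references to completed assessments are compatible with drafting after data collection but do not prove it.
- A reader might count three primary measures and say that a third of the primary evidence is lost, or put the alcohol false-positive rate as high as 1 − 0.95² = 9.75%. The count ignores the protocol's own numbering. The rate presupposes a choice made after seeing both results, an alpha that the documents do not state, and independence between two summaries of the same calendar, which is implausible.

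**Conclusion.** The mismatch is real and should be reconciled before unblinded analysis. It affects one of the two measures in the second co-primary outcome, and this conclusion rests on the text alone. The risk of selective outcome reporting follows from an unexplained removal at a time when some baseline information was known. It is a risk that readers cannot exclude, not an established act, and it does not by itself invalidate the grams-per-week result. The error-rate figures show only what restoring HDD would cost under an assumed alpha. The finding does not depend on them.

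**What to change.** Restore HDD in the SAP under co-primary alcohol use, and state:

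- the definition of a heavy drinking day, including its threshold;
- how HDD is derived from the existing TLFB calendar, and the observation window at each assessment;
- the analysis set (the same ITT set as grams per week) and a model suited to counts or proportions of days, for example a negative-binomial mixed model with days observed as offset, or a binomial mixed model with days observed as denominator;
- the treatment contrast and time point that carry the conclusion, since the SAP names a treatment-by-time interaction but no specific contrast;
- the place of HDD relative to CAPS-5 and grams per week, with the alpha and the multiplicity rule. The SAP has no co-primary decision rule for HDD to join, so one must be written.

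If the sponsor prefers grams per week as the only primary alcohol measure, it should record a change with its date, reason and blinding status before unblinded analysis, and report HDD as a named secondary outcome with the same definition and model.

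The cost is SAP text and one more model, with no new data collection. If HDD becomes a separate primary test, there is also the multiplicity cost shown above, which the stated rule would have to control.

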#### ***Screening, after 8 weeks of stable levels of any medication (week 0)***

##### ***Interview and assessments***

Demographic data, PTSD and alcohol use (structured interview)

PTSD diagnosis and symptom severity (CAPS-5, PCL-C)

Anxiety symptom severity (BAI or STAI)

Depression symptom severity (BDI-II)

Alcohol consumption during the past 90 days (TLFB)

Alcohol craving (PACS)

Alcohol dependence severity (ADS, AUDIT)

Level of function in important areas of life (ASI-SR)

Clinical Global Impression (CGI)

Intelligence (Matrigma)  
Personality (NEO-FFI-3)  
Health care consumption (TIC-P)  
Treatment credibility/expectancy (The Credibility/Expectancy Questionnaire)  
Working alliance (WAI-S)

*Biological samples*

Blood samples: complete blood count (Hb, MCV, TPK, LPK), liver function tests (ASAT, ALAT, GGT), alcohol marker (PEth), DNA-extraction  
Cortisol in hair  
Urine screening for alcohol and illicit drugs (U-Etg etc.)

Randomisation

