***Treatment (week 1-12, to be completed over a maximum of 20 weeks)***

*Assessments*

PTSD-symptom severity (PCL-C)  
Anxiety symptom severity (STAI)  
Depression symptom severity (BDI-II)  
Alcohol consumption (TLFB)  
Alcohol craving (PACS)

*Biological samples*

Urine screening for alcohol and illicit drugs (U-Etg etc.)

*Treatment*

COPE or RP (Project MATCH 12 sessions)

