***Follow up - at each session, after session 6 and 12 and six and nine months post baseline***

Prior to each COPE or RP session, each subject will fill out self-assessment forms on PTSD-symptom severity (PCL-C), alcohol consumption (TLFB), alcohol craving (PACS), anxiety symptom severity (STAI) and depression symptom severity (BDI-II). For information on follow ups at sessions 6 and 12 and six and nine months post baseline, see summary above on pages 8-10.

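### The alcohol model pools 90-day recalls with roughly weekly session values under one residual variance and never defines weekly grams per row, so its standard errors can be materially wrong in either direction.

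*Combined protocol and SAP*

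**What the plan says.** The SAP, under Alcohol use, defines the outcome as "Difference in grams of alcohol consumed per week, measured using Timeline Follow Back (TLFB), between groups up to 9-month follow-up". It takes "Data from baseline, sessions 1-12, 6- and 9-month follow-ups when TLFB was completed", which makes 1 + 12 + 2 = 15 occasions in one model. That model has treatment, time, their interaction and a random intercept, and "a first-order autoregressive covariance matrix are to be used". No variance specific to visit or window is mentioned.

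The recall periods are in the protocol. The screening list (week 0) has "Alcohol consumption during the past 90 days (TLFB"), and the list for six and nine months repeats the same 90 days. The treatment-phase list has only "Alcohol consumption (TLFB") with no period. The follow-up section says "Prior to each COPE or RP session, each subject will fill out self-assessment forms on PTSD-symptom severity (PCL-C), alcohol consumption (TLFB"), again with no period. The Summary describes sessions as typically weekly, but the treatment phase is "to be completed over a maximum of 20 weeks". Follow-ups fall at about weeks 26 and 38.

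Neither document says whether weekly grams at a 90-day occasion is the mean over 90 days or the last 7 days, what days a session value covers, how days reported twice are handled, or how time is coded.

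**The concern.** A mean over about 13 weeks varies less than a value from about one week. A single residual variance across all 15 rows is a compromise dominated by the 12 session rows, and it is then applied to contrasts that rest on the three 90-day rows. The standard errors of the treatment-by-time contrasts, which are the co-primary result, depend on that compromise.

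Three smaller matters follow from the same gap.

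- Because the form is completed before each session, the session 1 value describes drinking before any therapy, and it has no previous session from which to count.
- Twelve sessions can take 12 to 20 weeks, so session number and calendar time may differ widely between women.
- A 90-day look-back from week 26 can reach into treatment, so the same days could enter both a session row and the 6-month row.

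The SAP commits to one pre-selected model per outcome. Two analysts could nevertheless derive different co-primary values from the same calendars.

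**Working it through.** **Inputs from the documents.** 15 rows; 90-day recall at three of them; sessions about weekly; therapy up to 20 weeks; follow-ups at about weeks 26 and 38. No SD, intraclass correlation, alpha or power is given for alcohol use, so there is no planned figure to reproduce.

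**Assumptions (not in the documents).** 90 days = 13 weekly bins; a session value covers one week; share *s* of weekly variance that is stable between women, 0.3 to 0.7; week-to-week autocorrelation ρ of the rest, 0 to 0.6; categorical time, AR(1) by visit order, complete data. Sensitivity sets make 0.2 to 0.4 of the variance slow within-person drift (autocorrelation 0.95 per week), or make the baseline SD 1.5 or 2 times the later SD, or both.

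**Step 1: variance of a 90-day mean relative to a weekly value.** Ratio = s + (1 − s)·f, with f = (1/13)[1 + 2Σ(1 − k/13)ρ^k], k = 1 to 12.
- ρ = 0, s = 0.3: f = 1/13 = 0.077; 0.30 + 0.70 × 0.077 = 0.35.
- ρ = 0.6, s = 0.7: f = 0.263; 0.70 + 0.30 × 0.263 = 0.78.

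**Step 2: a case that can be done by hand (ρ = 0, no drift).** Set the within-woman weekly variance to 1. Twelve rows have variance 1 and three have 0.077. The pooled value is (12 + 3 × 0.077)/15 = 0.815. The random intercept cancels from change contrasts.
- Baseline to 9 months: model 2 × 0.815 = 1.63; true 2 × 0.077 = 0.154; SE ratio √(1.63/0.154) ≈ 3.26 (likelihood fit: 3.25).
- Baseline to session 12: model 1.63; true 1 + 0.077 = 1.077; ratio √1.51 = 1.23.
- Session 1 to session 12: model 1.63; true 2; ratio √0.815 = 0.90. A nominal 5% test then has size 2Φ(−1.96 × 0.90) ≈ 8%.

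**Step 3: the planned covariance fitted by Gaussian likelihood to each assumed truth.** Entries are model SE / true SE of the between-arm contrast.

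| Window at baseline, 6 and 9 months | Assumed truth | Baseline to 9 months | Session 1 to 12 |
|---|---|---|---|
| 90-day mean | no drift, equal SD | 1.74–3.25 | 0.89–0.90 |
| 90-day mean | slow drift, equal SD | 1.21–1.54 | 0.90 |
| 90-day mean | baseline SD × 1.5 | 0.92–1.56 | 0.92–0.93 |
| 90-day mean | baseline SD × 2 | 0.72–1.04 | 0.96–1.00 |
| 7 days | no drift, equal SD | 0.99–1.00 | 0.99–1.00 |
| 7 days | slow drift, equal SD | 0.87–0.93 | 0.99 |
| 7 days | baseline SD × 1.5 to 2 | 0.60–0.80 | 1.05–1.17 |

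The rows with a larger baseline SD include sets with and without drift. With 90-day means, 0.72 occurs in one set; the next lowest is 0.77. In the first row, the joint treatment-by-time test has type I error of about 5.7% to 6.4%.

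**Step 4: overlapping days.** The 6-month look-back starts at day 26 × 7 − 90 = 92, just after week 13 (day 91). If session 12 falls at week *w*, the shared days are max(0, 7w − 92): week 13, 0; week 14, 6; week 16, 20; week 18, 34; week 20, 48 (48/90 = 53%). The 9-month look-back starts at day 38 × 7 − 90 = 176, so at nominal timing the two follow-ups share 182 − 176 = 6 days.

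**The case against.** The best defence is that the documents give a recall period, not an averaging rule. The TLFB is a daily calendar, so a last-7-days value could be taken at every occasion, and the SAP does not exclude this. That stands: 90-day averaging, the one-week session value and time indexed by session number are all inferences. It does not rescue the plan, because a rule that decides the co-primary values should be written down, and the 7-day rows of the table still depart from 1 when baseline spread is larger or drift is slow.

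A reader might infer that the standard errors are certainly too large and that power is lost. The documents do not support this. They give no variance components, and under plausible ones the ratio for baseline to 9 months lies on either side of 1. The SAP also names no single contrast. Baseline to 9 months is among the worst affected, while the joint interaction test stays fairly near 5% in the no-drift sets.

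A reader might also infer that drinking days are counted twice as a rule. Sessions are typically weekly, and a woman who finishes by week 13 contributes no session day to the 6-month window. The 48 days are the extreme that the 20-week limit permits; the documents do not say how many women run late.

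Lastly, a pre-therapy session 1 row is not in itself an error. With categorical time it is one more time point in both arms, and the SAP does not label it on-treatment.

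**Conclusion.** The concern holds in conditional form. The documents establish different recall arrangements, one model for all 15 occasions, and no rule for derivation, overlap or time scale. A single residual variance is the ordinary reading of the stated matrix. If 90-day means are used, the model SE for baseline to 9 months can be about 0.8 to 3.3 times the true SE (0.72 in the most extreme set), and about 0.9 times for session 1 to session 12. These figures rest on assumed variance components and complete data; they show possible size, and the direction is not fixed. Overlap between session days and the 6-month window arises only when therapy runs past about week 13. This is more than missing detail, because the stated covariance can give wrong error bars under either derivation.

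**What to change.** In the SAP section on alcohol use:

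1. State, for each of the 15 rows, the days covered and the formula for weekly grams.
2. Use each calendar day once, for example by starting the 6-month value after the last session-covered day, with a matching rule for the two follow-ups. For a week-20 finisher this leaves 90 − 48 = 42 days, so the rule must allow for shorter windows.
3. Label the session 1 value as pre-therapy and say which days it covers.
4. Replace the homogeneous AR(1) with visit-specific variances and correlation based on weeks since randomisation. Separate residual variances for 90-day and session rows are the minimum. They deal with window length but not with a larger baseline spread, so baseline should preferably have its own variance.

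A fully unstructured matrix on 15 rows has 15 × 16/2 = 120 parameters, too many for about 120 completers. An alternative is a small set of window means with an unstructured covariance; five windows need 15 parameters. That choice is a preference: calendar windows would not coincide with the protocol's session 6 and session 12 occasions, and the session-by-session curve would become descriptive.

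The cost is reprogramming the TLFB derivation, SAP wording and a few more covariance parameters. No new data are needed, since the TLFB is already recorded by day.

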## Secondary outcomes

### Self-rated PTSD symptom severity

Measured using the PTSD Checklist – Civilian version (PCL-C), range 17-85. To be analyzed using an LMM with fixed effects for treatment, time and their interaction, a random effect for subjects and a random intercept. Restricted maximum likelihood estimation, Satterthwaite approximation, and a first-order autoregressive covariance matrix are to be used.

Data from baseline, sessions 1-12, 6- and 9-month follow-ups when PCL-C was completed.

ITT and modified ITT as above.

### A biomarker of alcohol use

A biomarker of alcohol use (PEth) in blood. To be analyzed using an LMM with fixed effects for treatment, time and their interaction, a random effect for subjects and a random intercept. Restricted maximum likelihood estimation, Satterthwaite approximation, and a first-order autoregressive covariance matrix are to be used.

Data from baseline, mid-treatment (session 6) and the last treatment session (session 12), 6- and 9-month follow-ups when blood samples were taken.

ITT and modified ITT as above.

